### Primary outcome

The primary outcome is the difference in skill performance of BAC between the two groups at post-training, assessed using a previously validated 7-point global rating scale (GRS) [22, 39]. Video recordings will be scored by three independent airway experts (2 Royal College certified emergency physicians, 1 staff anesthesiologist) trained in BAC. All reviewers will receive training from study investigators followed by practice video review to ensure scoring standardization. All reviewers will be blinded to the subjects’ identities and group allocation.

### Secondary outcomes

Secondary outcomes include participant feedback and chronometry after the initial training and retention sessions. Performance time begins when the participant first palpates the neck of the task trainer and ends with successful ventilation. Time scores will be measured using video review. Participant feedback will be collected with pre and post-training surveys. Skill performance (measured using GRS) at 6–12 months will also be compared.

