**Fig. 1 Fig1:**
[figure not shown]
Deliberate practice model. Deliberate practice occurs over time with repeated feedback and refinement of microskills, combined together resulting in improved task completion

Some authors suggest that simulation training using DP + ML results in superior outcomes compared to other methods of simulation-based practice [2]. An alternative to DP + ML is self-guided practice (also referred to as self-directed or self-regulated) whereby “*individuals take the initiative, with or without the help of others in diagnosing their learning needs, formulating learning goals, identifying human and material resources for learning, choosing and implementing appropriate learning strategies, and evaluating learning outcomes*” [18]. The few studies that compare DP with self-guided practice yielded mixed results while also limited by both small sample sizes and generalizability of a single institution setting [8, 19].

An important confounding factor that may explain these discrepant results is the variability in how DP is applied during SBME. Deliberate practice is often described in the context of sustained investment in practice over long periods of time in order to attain expert status [9]. In medical training, this can be difficult given the wide breadth of skills and knowledge that are required, especially when it comes to rarely performed procedures. While most clinical educators adhere to the key components of Ericsson’s criteria, in real practice, training is condensed over a shorter time-frame. The goal of the current study therefore is to explore the application of DP in a realistic context in order to understand how it is best optimized in curricular design, particularly for the acquisition of a rarely performed technical skill in the emergency medicine setting. Our study design incorporates several metrics of performance including a global rating scale and chronometry measured both immediately after and 6–12 months following skill instruction.

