### Instructional methods

Residents at each study site will be assigned to receive either DP + ML, or self-guided practice using a computer-generated randomization process. Participants will be blinded to the study group assignments. For practical purposes, we will cluster 4–6 participants with 1 instructor who will facilitate the training using one of the two instructional methods. This group size aligns with recommendations from surgical education literature for procedural skill training that demonstrates the optimal trainee:instructor ratio for procedural skills training [37]. All instructors are board certified emergency physicians with expertise in procedural skill training. Prior to the session, each instructor will receive an introduction to the task trainer, a briefing on how to conduct the training and a standardized approach to BAC performance. The instructors assigned to the DP + ML session will also receive an introduction to the BAC checklist and explicit instructions to facilitate mastery learning followed by deliberate practice [38]. The instructors assigned to the self-guided practice session will be told explicitly that they can only provide feedback following a participant request. They will be instructed by the study investigators on the necessary steps for BAC performance.

Both groups will receive an introductory lecture to surgical airway performance and a demo of the BAC on the task trainer by the session instructor. Participants will then complete a pre-training survey assessing self-confidence and prior cricothyroidotomy experience, followed by a video-recorded performance of a BAC using an upper body task trainer (head and neck from a Laerdal SimMan) to assess baseline performance before training begins.

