### Sample size determination

A justification of sample size requires knowledge of results from similar studies. As there have been no studies of this exact design conducted previously we have used a sample size formula to evaluate our proposed sample size [40]. We base the sample size calculation on assumptions inherent of a between groups comparison [40]. Given the multi-site nature of this study, there will be approximately 16–20 participants in each site; for a total of 80 in each group. At 80 participants in each group, there is sufficient power (80%) to detect a difference in GRS score of 1.3 between groups, assuming α = 0.05 and β = 0.2 to detect. Similar approaches have been used by Freidman et al. [39] and Naik et al. [41].

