### Statistical analysis

The survey data will be analyzed using descriptive statistics. The primary outcome (GRS) score will be evaluated using a repeated measures ANOVA with between subject factor of instruction (DP + ML or SG group) with one within subject factor of assessment repeated 3 times (pre, post, and retention). SPSS software (SPSS Inc. 18.0, Chicago IL) will be used for data analysis. 2-sided *P* < 0.05 is considered statistically significant for the primary outcome. Interrater reliability (IRR) for the reviewers’ scores will be analyzed using an intraclass correlation, after reviewing the same 20 videos. If a target IRR of ≥0.7 is achieved, the rest of the videos will be scored by one reviewer. Confidence ratings will be compared with GRS at pre-training, post-training and retention using Spearman’s correlations.

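### Performance time is scheduled only after training and at retention, leaving the filmed pre-training attempt unused as a baseline for this secondary outcome

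*Protocol article*

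**What the plan says.** All places are in the protocol article.

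- **Secondary outcomes** gives the time points for performance time: "Secondary outcomes include participant feedback and chronometry after the initial training and retention sessions". It also gives the start and stop rule, "Performance time begins when the participant first palpates the neck of the task trainer and ends with successful ventilation", and the source: "Time scores will be measured using video review".
- **Background**, at the end of the subsection on deliberate practice and mastery learning, gives the same two time points in its summary of the design: "chronometry measured both immediately after and 6–12 months following skill instruction".
- **Instructional methods** has both groups complete a survey, "followed by a video-recorded performance of a BAC using an upper body task trainer". The stated purpose of that recording is "to assess baseline performance before training begins".
- **Statistical analysis** puts the pre-training assessment into the GRS model, with "one within subject factor of assessment repeated 3 times (pre, post, and retention". It describes no analysis of performance time.

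**The concern.** Two performance measures can be taken from the same recordings. One, the GRS, has a pre-training value in its analysis. The other, time, has none in its schedule, and no reason is given. The background presents time as an important metric for time-sensitive procedures, and this procedure was chosen partly because it is time-sensitive.

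Two things are at stake:

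- **Precision.** Residents from PGY1 to PGY5 are enrolled with no exclusion criteria. If they differ in speed before training and the difference persists, it stays in the error term when time is compared between groups.
- **Description.** Without a pre-training time, the report cannot show how much each method shortened the procedure, or whether speed at 6–12 months has drifted back towards its starting level. Retention is one of the stated objectives.

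**Working it through.** **Step 1. Is a baseline time obtainable?** A pre-training attempt is filmed in both groups (Instructional methods), and time is read from video with a defined start and stop (Secondary outcomes). So it is obtainable for every attempt that reaches ventilation. For an attempt that does not, the stop rule yields no value.

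**Step 2. Is it planned?** Both places that give time points for chronometry name post-training and retention only. The Statistical analysis section is silent on time. A baseline time is therefore neither scheduled nor ruled out.

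**Step 3. What is it worth?** The article states no power or precision figure for time, so there is none to reproduce. Its 80% power statement concerns the GRS. The inputs are:

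- 80 residents per group (Sample size determination).
- Two-sided 5% level and 80% power. The article states these for the GRS; they are used here only as a yardstick.
- r, the correlation between baseline time and later time. It is not in the article and is assumed.

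The detectable difference without a baseline, in SD units, is (1.960 + 0.842) × √(2/80) = 2.802 × 0.1581 = 0.443.

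With baseline time as a covariate, the variance of the group difference is multiplied by 1 − r². The detectable difference becomes 0.443 × √(1 − r²), and the equivalent group size is 80 / (1 − r²).

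| r (assumed) | Variance reduction (r²) | Detectable difference (SD) | Equivalent n per group | Power at 0.443 SD |
|---|---|---|---|---|
| 0 | 0% | 0.443 | 80 | 80.0% |
| 0.1 | 1% | 0.441 | 81 | 80.4% |
| 0.3 | 9% | 0.423 | 88 | 83.6% |
| 0.5 | 25% | 0.384 | 107 | 89.9% |

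The table treats all 160 residents as independent, with both times observed.

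**Step 4. What shrinks the gain?**

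- *Failed baseline attempts.* Suppose a share f of residents has no baseline time and the not-achieved indicator itself explains nothing. The reduction is then about (1 − f) × r², so half failing would halve it.
- *Extra terms.* With 160 residents, each added term costs about 1/160 ≈ 0.6% in variance. At r = 0.1 this roughly cancels the gain.
- *Instructor groups.* Residents train in groups of 4–6 with one instructor. Variation between instructors would not necessarily shrink with a resident's baseline time.

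**Step 5. Covariate or change score?** A change-from-baseline comparison has a variance ratio of 2(1 − r) against the unadjusted one. That is 1.8 at r = 0.1, 1.4 at 0.3 and 1.0 at 0.5. Below r = 0.5 a change score loses precision, whereas the covariate costs no more than its extra terms.

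**The case against.** The strongest reply is that listing an outcome at post-training and retention does not, in this article, mean that no baseline is used. The Primary outcome section defines the GRS at post-training only, and the Background sentence gives the GRS the same two time points as chronometry. Yet the Statistical analysis section uses a pre-training GRS. The pre-training video is meant to capture baseline performance in general and is not reserved for the GRS. No analysis of time is described, and an analysis plan not shown could time those videos and adjust for the result.

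This stands against any claim that time *cannot* be adjusted for baseline, or that change *cannot* be reported. A reader might infer either from the schedule, but the recordings will exist and can be timed later. It does not remove the narrower point: the GRS has its baseline use written down and time does not.

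Two further objections also stand in part. The Discussion expects the rarity and novelty of the procedure to keep differences in prior experience small, which points to a low r. That remark concerns experience with this procedure rather than general procedural speed, so it does not settle the matter. Secondly, some early attempts may never reach ventilation and so have no time. The baseline is therefore not entirely free: it needs a rule for failures. The same stop rule raises that question at the other two assessments.

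**Conclusion.** The point holds as a cheap improvement to a secondary outcome. The schedule as written leaves an available baseline unused. That forgoes some precision in the between-group comparison of time and any account of how much each method shortens the procedure.

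The size cannot be fixed from the article. Under assumed correlations the variance reduction is about 1% at 0.1, 9% at 0.3 and 25% at 0.5, and smaller if many baseline attempts fail. These figures assume independent residents with usable times. The correlation with retention, 6–12 months later, need not equal that with post-training time.

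Three stronger readings are tempting and unsupported:

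- *That the comparison of time is biased.* Randomisation keeps it valid without adjustment, and chance imbalance in starting speed is already reflected in its interval.
- *That the loss amounts to 10–56% of the sample.* That is 1/(1 − r²) − 1 for r from 0.3 to 0.6. It leaves out low correlations and presumes a baseline time for every resident.
- *That precision is lost for nothing.* A baseline time needs a failure rule and extra readings.

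**What to change.** Add pre-training to the time points for performance time, read from the existing baseline videos with the same start and stop rule. When comparing time between groups at post-training and at retention, include baseline time as a covariate and do not analyse change scores. Keep residents who did not reach ventilation at baseline in the analysis through a not-achieved indicator, with baseline time set to a fixed value for them. Summarise pre-training time by group, with the number who did not ventilate, so that the report can describe how far each method shortened the procedure.

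The cost is about 160 extra readings from videos already made, and one or two extra model terms. No new session or procedure is needed, and neither the primary outcome nor the sample size changes.

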### Sample size determination

A justification of sample size requires knowledge of results from similar studies. As there have been no studies of this exact design conducted previously we have used a sample size formula to evaluate our proposed sample size [40]. We base the sample size calculation on assumptions inherent of a between groups comparison [40]. Given the multi-site nature of this study, there will be approximately 16–20 participants in each site; for a total of 80 in each group. At 80 participants in each group, there is sufficient power (80%) to detect a difference in GRS score of 1.3 between groups, assuming α = 0.05 and β = 0.2 to detect. Similar approaches have been used by Freidman et al. [39] and Naik et al. [41].

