**Methods:**

A multi-centre, randomized study will be conducted at four Canadian and one American residency programs with 160 residents assigned to either mastery learning and deliberate practice (ML + DP), or self-guided practice for BAC. Skill performance, using a global rating scale, will be assessed before, immediately after practice, and 6 months later. The two groups will be compared to assess whether the type of practice impacts performance and skill retention.

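### The stated 80% power for a 1.3-point GRS difference implies an SD of about 2.9, which is not credible if the 7-point scale is scored 1 to 7

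*Protocol article*

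**What the plan says.** The Abstract (Methods) plans for "160 residents assigned to either mastery learning and deliberate practice (ML + DP), or self-guided practice for BAC". The section Sample size determination says "we have used a sample size formula to evaluate our proposed sample size", and describes the basis of the calculation in these terms: "We base the sample size calculation on assumptions inherent of a between groups comparison". It sets the size at 80 per group and claims that "there is sufficient power (80%) to detect a difference in GRS score of 1.3 between groups". The error rates behind that claim are an alpha of 0.05 and a beta of 0.2. The Statistical analysis section makes the test two-sided: "2-sided *P* < 0.05 is considered statistically significant for the primary outcome".

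Under Primary outcome, post-training performance is "assessed using a previously validated 7-point global rating scale (GRS", with two references. The anchors are not given, nor whether the score is one rating or a combination of items.

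The sample size section gives no SD, standardised effect, design effect or allowance for loss. It also puts roughly 16 to 20 participants at each site, and the Study design and setting section lists five sites.

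**The concern.** Group size, alpha, power and difference are all fixed, so the one missing quantity, the SD, follows by algebra. It comes out very close to the largest SD that a 1 to 7 score allows. The point is therefore more than an SD left out of a condensed article: the figures that are printed do not sit comfortably with the scale that is printed.

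This paragraph is the article's only quantitative justification for the trial's size. The Discussion faults earlier comparisons for small samples and offers this trial as the large-sample answer. A reader who takes 1.3 points as the trial's resolution would misjudge what a null result rules out. Nor can the reader tell whether 80 per group is generous or tight for the difference of interest.

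**Working it through.** **Inputs.** From the article: n = 80 per group, difference 1.3, alpha 0.05 two-sided, power 80%, plain between-group comparison. Assumed: GRS scored 1 to 7. Not given: SD.

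**1. The plan's own figure.** It cannot be reproduced directly because there is no SD, so solve for the SD.

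- Normal approximation: SD = 1.3 / [√(2/80) × (1.960 + 0.842)] = 1.3 / (0.1581 × 2.802) = 2.93 to 2.94.
- Two-sample t-test: the detectable effect is d = 0.446, so SD = 1.3 / 0.4457 = 2.92.

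Putting SD 2.92 back in returns 80% power, so the arithmetic closes.

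**2. Is that SD possible on a 1 to 7 score?** For a given mean μ, the SD is largest when every score is 1 or 7: SD = √[(μ − 1)(7 − μ)].

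- Overall maximum, at μ = 4: √(3 × 3) = 3.0.
- Two means 1.3 apart, placed symmetrically at 3.35 and 4.65: √(3.65 × 2.35) = √8.58 = 2.93 in each group.
- Two means off centre, for example 5.0 and 6.3: √(4 × 2) = 2.83 and √(5.3 × 0.7) = 1.93, so the ceiling is lower.
- Even spread over all seven categories: 2.0.

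Even in the most favourable placement there is almost no slack. The variance ceiling is 8.578 and the implied variance is 2.917² = 8.509, a gap of 0.069. A score of 2 or 6 uses up (7 − 6)(6 − 1) = 5 units of that gap, and more central scores use more. At most 0.069 / 5 = 1.4% of scores could then be anything other than 1 or 7.

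**3. What 80 per group gives for other SDs** (t-test, no clustering allowance; the SDs are assumptions). Detectable difference = 0.4457 × SD.

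| Assumed SD | Detectable at 80% power | Power for 1.3 | n per group needed for 1.3 |
|---|---|---|---|
| 1.0 | 0.45 | >99.9% | 11 |
| 1.5 | 0.67 | >99.9% | 22 |
| 2.0 | 0.89 | about 98% | 39 |
| 2.5 | 1.11 | about 90% | 60 |

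The normal approximation changes these by at most 0.01 points and one participant.

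**4. Could an unstated design effect explain 1.3?** Residents are trained in groups of 4 to 6 per instructor (Instructional methods). The design effect is 1 + (m − 1) × ICC, and the one needed is (2.917 / SD)².

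- For SD 1.5: (2.917 / 1.5)² = 3.78, so ICC = 2.78/5 to 2.78/3 = 0.56 to 0.93 for m = 6 to 4.
- For SD 2.0: (2.917 / 2.0)² = 2.13, so ICC = 1.13/5 to 1.13/3 = 0.23 to 0.38.

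**5. Per-site count.** Over five sites, 5 × 16 = 80 and 5 × 20 = 100 in total, not 160. The text agrees with 80 per group only if the count means per group at each site.

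**The case against.** The best defence has four parts.

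*The SD is missing, so the figure is uncheckable rather than wrong.* This stands in part. A reader might infer that the stated pair is impossible, but 2.92 lies just under 2.93. It is implausible on a 1 to 7 score, not excluded.

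*The GRS may combine items over a wider range.* This stands. The article does not describe the scoring, and on a wider scale an SD near 2.9 would give exactly the stated 80%. A reader might go on to infer that the claim fails on a summed score too. That would need a larger SD, and nothing in the article supports one.

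*An allowance for clustering may have been made without being reported.* This is possible but weak. The text describes a plain between-group calculation, and step 4 shows that a large ICC is needed even for an SD of 2.0. Loss to follow-up helps little, because the primary outcome is recorded immediately after practice.

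*The error is on the safe side.* This stands on the 1 to 7 reading. For any SD below 2.9 the plain calculation gives more than the claimed power.

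**Conclusion.** The point holds in a limited form and should be fixed. As a plain two-group calculation, 80 per group, 1.3 points and 80% power require an SD of about 2.9. If the GRS is scored 1 to 7, that is at the ceiling of what is possible and not credible. With an assumed SD of 1.0 to 1.5, the detectable difference is 0.45 to 0.67 points, so the stated 1.3 is about two to three times too coarse (1.3 / 0.67 = 1.9; 1.3 / 0.45 = 2.9).

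The conclusion rests on the 1 to 7 scoring and on no undisclosed design effect. If the score is a wider sum with an SD near 2.9, the stated figure would be right.

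Two stronger readings are not supported. One is that the trial is too small: on the 1 to 7 reading, before clustering, the error runs the other way. The other is that 1.3 was worked out for a different group size. At 16 to 20 per group, 1.3 points would imply an ordinary SD of 1.27 to 1.43, which is suggestive given the per-site count, but the article does not show that this happened.

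**What to change.** Revise the Sample size determination paragraph as follows:

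- State the GRS range and how it is scored, and the SD used, or an SD range with its basis.
- Give the detectable difference for 80 per group as about 0.45 SD (two-sided alpha 0.05, 80% power) before any clustering allowance, and convert it to points. On a 1 to 7 score that is, for example, 0.45 to 0.67 points for SD 1.0 to 1.5 and 0.89 for SD 2.0.
- Correct the 1.3 figure unless a stated SD or design effect reproduces it. If a clustering allowance was made, give the group size and ICC.
- Say whether the 16 to 20 participants are per site or per group at each site, so that the count agrees with 80 per group and 160 in total.

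The cost is one reworded paragraph and one recalculated figure. Enrolment, randomisation, outcome and test are unaffected.

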### Statistical analysis

The survey data will be analyzed using descriptive statistics. The primary outcome (GRS) score will be evaluated using a repeated measures ANOVA with between subject factor of instruction (DP + ML or SG group) with one within subject factor of assessment repeated 3 times (pre, post, and retention). SPSS software (SPSS Inc. 18.0, Chicago IL) will be used for data analysis. 2-sided *P* < 0.05 is considered statistically significant for the primary outcome. Interrater reliability (IRR) for the reviewers’ scores will be analyzed using an intraclass correlation, after reviewing the same 20 videos. If a target IRR of ≥0.7 is achieved, the rest of the videos will be scored by one reviewer. Confidence ratings will be compared with GRS at pre-training, post-training and retention using Spearman’s correlations.

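### The three-time-point repeated measures ANOVA named for the primary outcome does not test the post-training difference that the protocol defines as primary

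*Protocol article*

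**What the plan says.** Four statements in the protocol article's Methods bear on this.

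- **Primary outcome:** "The primary outcome is the difference in skill performance of BAC between the two groups at post-training". This is one quantity at one time point.
- **Secondary outcomes:** "Skill performance (measured using GRS) at 6–12 months will also be compared". Retention is therefore secondary.
- **Instructional methods:** the pre-training video is recorded "to assess baseline performance before training begins". It is a baseline.
- **Statistical analysis:** the primary outcome is "evaluated using a repeated measures ANOVA with between subject factor of instruction (DP + ML or SG group"). To this the section adds a repeated factor, described as "with one within subject factor of assessment repeated 3 times (pre, post, and retention"). The decision rule follows: "2-sided *P* < 0.05 is considered statistically significant for the primary outcome".

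Sample size determination rests on a simple two-group comparison: "At 80 participants in each group, there is sufficient power (80%) to detect a difference in GRS score of 1.3 between groups". The Statistical analysis section does not say whether the main effect, the interaction or a contrast decides the primary outcome, and it specifies no contrast at post-training.

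**The concern.** The primary outcome and the sample size both concern a single between-group difference after training. The named analysis spans three time points, one of which cannot carry a treatment effect and one of which is a secondary outcome. The model yields two F-tests that involve group, and neither targets the stated difference.

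- **Instruction main effect.** It compares the arms on each participant's average over pre, post and retention. A real post-training benefit is diluted by the baseline, and further by any loss of benefit by 6–12 months.
- **Group-by-time interaction.** It asks whether the arms' profiles differ anywhere across the three times. A difference confined to retention can make it significant.

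The trial's one confirmatory P value could therefore miss a real immediate benefit, or be declared positive when the arms do not differ at post-training.

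**Working it through.** **Inputs from the protocol article.** n = 80 per arm, detectable difference 1.3 GRS points, two-sided α = 0.05, 80% power. No SD and no correlation between assessments is given.

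**Assumptions.** Equal SD σ at each time, a common within-person correlation ρ of 0.2, 0.3, 0.5 or 0.7, no dropout, independent participants, and no true difference at baseline.

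**Step 1: the stated power.** It cannot be reproduced without an SD, so solve for the SD it implies:

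σ = 1.3 × √(80/2) / (1.960 + 0.842) = 8.222 / 2.802 = 2.93, a standardised difference of 1.3/2.93 = 0.44.

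This fixes the benchmark: a post-training difference for which a direct two-group test has the stated power. The exact t-test value is 79.5%.

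**Step 2: what the main effect estimates.** Let D be the post-training difference and k the fraction retained. The averaged difference is (0 + D + kD)/3:

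- k = 0: D/3 = 0.43
- k = 0.5: D/2 = 0.65
- k = 1: 2D/3 = 0.87

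This step needs no assumed SD or correlation.

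**Step 3: power by noncentral F.** Here d_t is the group difference at time t and d̄ its mean over the three times.

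- Main effect: λ = d̄² × (n/2) / [σ²(1 + 2ρ)/3], df 1 and 158
- Interaction: λ = (n/2) × Σ(d_t − d̄)² / [σ²(1 − ρ)], df 2 and 316
- Post-training t-test: λ = D² × (n/2) / σ², df 1 and 158
- Post-training ANCOVA on the pre score: the t-test λ divided by (1 − ρ²), df 1 and 157

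Examples at ρ = 0.5, with σ² = 8.61:

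- Main effect, nothing retained: 0.433² × 40 / (8.61 × 2/3) = 1.31, power 21%
- Interaction, half retained: 40 × (0.65² + 0² + 0.65²) / (8.61 × 0.5) = 7.85, power 70%
- t-test: 1.69 × 40 / 8.61 = 7.85, power 79.5%
- ANCOVA: 7.85 / 0.75 = 10.47, power 90%

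| True pattern | Test | ρ = 0.2 | ρ = 0.3 | ρ = 0.5 | ρ = 0.7 |
|---|---|---|---|---|---|
| Post only (k = 0) | Main effect | 27% | 25% | 21% | 18% |
| | Interaction | 62% | 68% | 83% | 97% |
| Half retained (k = 0.5) | Main effect | 53% | 48% | 40% | 34% |
| | Interaction | 49% | 55% | 70% | 91% |
| Fully retained (k = 1) | Main effect | 78% | 72% | 62% | 55% |
| | Interaction | 62% | 68% | 83% | 97% |
| Any of the above | Post-training ANCOVA | 81% | 83% | 90% | 97% |
| Retention only, D = 0 at post | Main effect | 27% | 25% | 21% | 18% |
| | Interaction | 62% | 68% | 83% | 97% |
| | Post-training t-test or ANCOVA | 5% | 5% | 5% | 5% |

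**Step 4: simulation check** at ρ = 0.5, 3,000 trials per pattern. For post only, half retained, fully retained and retention only, the main effect rejected in 20%, 40%, 61% and 21%, and the interaction in 83%, 70%, 82% and 85%. The post-training t-test rejected in 79% under each of the first three patterns and in 5% under the last. These agree with the table.

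**The case against.** **The article names a model, not a deciding test.** A post-training group contrast is a routine follow-up within this ANOVA, and a condensed article may leave that choice to a fuller plan. It is true that the article does not say which test decides. But it does not leave the method open either: it gives the model, both factors, all three assessments and the significance threshold for the primary outcome. A later document naming a post-training contrast would change what decides the trial. Until then the published text allows the deciding test to be chosen after the data are seen.

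**Dilution belongs to the main effect.** This stands. At ρ = 0.5 the interaction beats the plain t-test when the benefit is wholly lost or wholly kept (83% against 79.5%), and at ρ = 0.7 it does so in all three patterns. It was still below ANCOVA in every benchmark case computed, and it does not isolate post-training.

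**The benchmark SD of 2.93 is very large for a 7-point scale.** This also stands. If the true difference is 1.3 and the SD is 2.0 (assumed), interaction power over ρ = 0.2 to 0.7 is 83% to nearly 100%. The main effect still has only 33–51% when nothing is retained. A smaller SD also makes the other error worse: with 1.3 at retention only, SD 2.0 and ρ = 0.3, λ = 40 × 1.127 / (4 × 0.7) = 16.1 and the interaction rejects in 96% of trials.

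**A retention-only difference is not an expected pattern.** Nothing in the protocol predicts it. Those figures show what the tests can respond to; they are not forecast error rates.

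**Using the baseline as an outcome is not an error in itself.** Agreed: in a randomised trial group-by-time is a valid analysis of change, and ANCOVA is mainly a gain in efficiency. The fault is that the analysis does not target post-training.

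**Conclusion.** The concern holds. The stated primary outcome is a single post-training difference, and the analysis attached to it yields two group-related tests, neither of which is that difference. The reduction of the main effect to between D/3 and 2D/3 follows from the design alone. At the benchmark effect, with ρ assumed between 0.2 and 0.7, power is 18–78% for the main effect and 49–97% for the interaction, against 81–97% for a baseline-adjusted post-training comparison. With no post-training difference and a same-size effect at retention, the interaction rejects in 62–97% of trials and the main effect in 18–27%, where a direct test holds 5%.

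The percentages depend on the assumed correlation, compound symmetry, no dropout and the benchmark effect size. The mismatch does not. Because it concerns the trial's one confirmatory decision, it should be settled before analysis.

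A related consequence: a standard repeated measures ANOVA uses complete cases. The Skill retention section expects scheduling difficulties at 6–12 months, so a resident with valid pre and post scores who misses that session would drop out of the primary analysis although the primary outcome was observed.

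**What to change.** In Statistical analysis, define the primary analysis as the comparison of post-training GRS between arms, adjusted for pre-training GRS. Use ANCOVA or the equivalent group contrast at post-training from a mixed model. Test it at two-sided 0.05 and report the adjusted mean difference with its 95% confidence interval. Keep the three-time-point model as a secondary analysis, with a separate, named contrast for retention.

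The smallest repair that would remove the mismatch is one sentence naming the post-training group contrast within the planned model as the sole primary test. The baseline-adjusted comparison is preferable because it is more efficient and does not require attendance at retention.

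The cost is one paragraph of text. The pre-training video is already collected, so no new data are needed.
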